## Methods/design

This protocol is reported in accordance with the Standard Protocol Items: Recommendations for Interventional Trials (SPIRIT) reporting guidelines [30] and the Consolidated Health Economic Evaluation Reporting Standards (CHEERS) [31]. A Project Steering Committee, comprising investigators, site clinicians and a consumer representative, will meet on a four-monthly basis to review trial progress. Any modifications to the trial protocol will be reported on the Australian and New Zealand Clinical Trials Registry (anzctr.org.au).

### Design

A stepped-wedge cluster randomised trial design will be conducted over 54 weeks, involving nine blocks of six-weeks duration (Fig. 1) [32]. Randomisation refers to the time when each ward crosses over from usual care to experimental conditions. Three months prior to trial commencement, a blinded researcher, not involved in the assessment or delivery of intervention, will randomise wards to the order of commencement of My Therapy using a computer-generated number sequence. Each ward will transition from the usual care condition (control group receiving usual care) to the experimental condition (intervention group receiving My Therapy in addition to usual care) sequentially at six-week intervals until all sites have crossed over to the experimental condition. Therapists and assessors will not be blind to group allocation and they will be informed of their upcoming cross over six weeks prior to cross over. This is due to the practical need to provide My Therapy education to the staff in the six weeks prior to commencing. In addition, patients will not be blind to group allocation due to the need to educate and engage patients in the My Therapy program.

**Fig. 1 Fig1:**
[figure not shown]
Timeline of program implementation

### Setting and participants

The project will take place within eight rehabilitation wards (totalling over 200 rehabilitation beds) across four Victorian health networks (see anzctr.org.au for study sites). At one health service, the two wards will incorporate home-based bed-substitution; all others will be located within inpatient facilities. We will include all patients aged 18 years or older undergoing rehabilitation on the selected rehabilitation wards during the trial period, of any rehabilitation diagnosis. Patients who do not speak English and those with a cognitive impairment will not be excluded. We will exclude any patients without coverage under Australia’s universal health care program (Medicare).

### Participant recruitment

This trial will use an opt-out approach for consent [33]. Throughout the 54-week study period, all patients admitted to a participating ward will be provided with a participant information sheet on admission. The form will explain the research project, how participant information will be accessed and used and how to opt-out if patients do not wish for their information to be used in this project. An interpreter will be accessed for patients with inadequate English. Next of kin will be contacted for all patients with a documented cognitive impairment who are unable to understand project involvement; next of kin may choose to opt-out on behalf of the patient. The project data of any patients who choose to opt-out will not be collected by researchers.

### Usual care and intervention (Table 1)

**Table 1 Tab1:** Description of experimental and control group conditions according to the template for intervention description and replication (TIDieR) [34]

	Intervention group under experimental conditions	Control group under usual care conditions
Brief name	My Therapy in addition to usual care rehabilitation	Usual care rehabilitation
Why	A higher dose of inpatient rehabilitation results in better patient and health service outcomes.	To provide a comparison with My Therapy.
What materials	In addition to usual care materials, patient information materials include a My Therapy explanation pack and an electronic or paper based My Therapy program. Additional materials include adjuncts to the recommended tasks and exercises such as written cognitive tasks, hand weights and resistance bands. Staff information materials include a My Therapy explanation pack and user guide.	Usual care materials may include exercise equipment, or equipment for practice of functional tasks, such as kitchen or bathroom facilities.
What procedures	On commencement of rehabilitation, the occupational therapist and physiotherapist will complete a full assessment of the patient and develop a rehabilitation plan that is guided by patient centred goals. Where it is deemed safe and appropriate, a sub-set of the supervised occupational therapy and physiotherapy exercises and activities will be provided to the patient to be practiced independently and outside of supervised sessions. To be classified as a self-management program, as is the case for My Therapy, it must include each of the following, (a) a written program, (b) therapist documentation of the program within the medical record, (c) a feedback mechanism to the therapist (e.g., a paper based or smart device tick sheet), and (d) will be actively monitored and progressed as clinically required. The exercises and activities will be delivered to patients via the online exercise prescription program, www.physiotherapyexercises.com (PTX). Following discussion and input from the patient, the treating clinicians will log into PTX, select the exercises and activities for each individual patient, and then send the My Therapy program to the patient’s own device (for example mobile phone, iPad, or laptop) via SMS or email, or the therapist will print out the My Therapy program as a booklet. While the My Therapy program will specify the number of repetitions and sets, the patient will decide what is done, how often and when. My Therapy can be updated as often as required. My Therapy will commence at the beginning of the rehabilitation admission. It will continue throughout the rehabilitation admission until the day of discharge, when appropriate and safe to do so.	On commencement of rehabilitation, the occupational therapist and physiotherapist will complete a full assessment of the patient and develop a rehabilitation plan that is guided by patient centred goals. The exercises and activities will be practiced with patients under therapist supervision. The program can be updated as required. It will commence at the beginning of the rehabilitation admission and continue throughout the rehabilitation admission until the day of discharge. Under usual care conditions, some therapists may provide self-management to some patients, representing heterogeneity of clinical practice. However, it is understood that prior to the My Therapy study at the participating sites, the provision of a self-management program (or components of a self-management program) was uncommon, clinician dependent and without systematic processes or monitoring. In this study, the provision of individual components of a self-management program is considered advice and education, not self-management. To be classified as a self-management program, as is the case for My Therapy, it must include each of the following, individual components, (a) a written program, (b) therapist documentation of the program within the medical record, (c) include a feedback mechanism to the therapist (e.g., a paper based or smart device tick sheet), and (d) be actively monitored and progressed and clinically required. The frequency of provision of self-management (as distinct from advice and education), under usual care conditions, will be assessed as a part of the Process Evaluation (Process Evaluation Protocol [36]).
Who provides	Registered occupational therapists and physiotherapists will complete the assessments, establish and progress the My Therapy program. They will be provided with study familiarisation, explanation and a user guide. All other members of the rehabilitation team, including nursing, medical and allied health assistants, will support the program through patient encouragement and conversation, however they will not progress exercises or supervise the practice.	Registered occupational therapists and physiotherapists will deliver usual care.
How provided	My Therapy is delivered to each patient by the occupational therapists and physiotherapists.	Usual care is individually tailored for each patient according to their rehabilitation goals and progressed throughout the rehabilitation admission.
Where (setting)	Independent practice of My Therapy can be completed in the patient’s room on the ward, the hallway, or other designated independent practice areas.	Most often completed in gyms or therapy rooms within rehabilitation hospitals.
When/how much (dose)	While a goal will be set for the amount of independent My Therapy practice, it is the patient who decides the number of sessions, the durations of the sessions and the number of repetitions.	Site-dependent, based on staff ratios and funding.
Tailoring	My Therapy is individually tailored for each patient according to their rehabilitation goals and progressed throughout the rehabilitation admission.	Usual care rehabilitation is individually tailored for each patient according to their rehabilitation goals and progressed throughout the rehabilitation admission.
Fidelity checking measures	Adherence and fidelity to the intervention will be assessed as a part of the Process Evaluation (Process Evaluation Protocol [36]).	Adherence and fidelity to usual care will be assessed as a part of the Process Evaluation (Process Evaluation Protocol [36]).

As part of usual care, a registered occupational therapist and physiotherapist employed by the health service will complete a full assessment of each patient, as per their routine procedures, and develop a rehabilitation plan that is guided by patient-centred goals. This is already routine practice at each of the participating sites. When wards transition to experimental conditions, all patients will continue with their usual rehabilitation plan; in addition, they will commence My Therapy. For My Therapy, the same occupational therapist and physiotherapist employed by the health service will provide patients with a sub-set of occupational therapy and physiotherapy exercises and activities to be practiced independently (where it is deemed safe and appropriate), outside of supervised sessions. These exercises and activities may be performed in the patients’ rooms on the ward or other designated independent practice areas. My Therapy will include (a) a written program, (b) therapist documentation of the program within the medical record, (c) include a feedback mechanism to the therapist (e.g., a paper based or smart device tick sheet), and (d) be actively monitored and progressed as clinically required.

The exercises and activities will be selected by the treating therapist from the available exercises within the online exercise prescription program, PTX found at www.physiotherapyexercises.com. Where a required exercise is not available, the therapist will upload additional customised exercises for use. Following discussion and input from the patient, the treating clinicians will log into PTX, select the exercises and activities for each individual patient, and then send the My Therapy program to the patient’s own device (for example mobile phone, iPad, or laptop) via SMS or email, or the therapist will print out the My Therapy program as a booklet.

The occupational therapist and the physiotherapist will collaborate to combine the discipline specific exercises and activities to ensure a co-ordinated approach. The recommended number of repetitions and sets of each exercise or task will be specified and can be updated by the occupational therapist and physiotherapist as often as required. While a goal will be set for the amount of independent practice, it is the patient who decides the actual number of sessions, the duration of the sessions and the number of repetitions that they complete, each day. This will be progressed as required throughout the rehabilitation admission.

Occupational therapists and physiotherapists will have regular daily contact with patients from Monday to Friday. Weekend occupational therapy and physiotherapy service provision varies from one health nextweek to the next and this ranges from no weekend service to a seven-day service. Additional materials will be provided free of charge to the patient. These include adjuncts to the recommended tasks and exercises, such as written cognitive tasks, adaptive equipment (e.g., long handled shoe horn; over-toilet frame), and therapy equipment (e.g., weights and resistance bands).

In the six weeks before crossover to the My Therapy intervention, occupational therapists and physiotherapists will be provided with a My Therapy explanation pack and a user guide, study familiarisation and education sessions, and interactive group discussions to co-design local implementation strategies. All other members of the rehabilitation team, including nursing, medical and allied health assistants, will attend the study familiarisation sessions and will be able to support the program through patient encouragement and conversation. However, they will not progress exercises or supervise the practice.

Where needed, there will be hospital/ward-based tailoring to adapt to the variety of settings, patient groups and therapy teams. For example, at the health service with home-based bed-substitution wards, the allied health assistant may deliver the paper-based My Therapy program to the patient and provide some education, when the occupational therapist or physiotherapist cannot do so in a timely manner. However, the allied health assistant will not supervise the My Therapy exercises, nor will they modify or progress the program. Adherence to the intervention will be assessed via the Process Evaluation Protocol [35].

Behaviour change by the patient and the therapist is key to successful implementation of My Therapy. Figure 2 describes the Why, What and How [36] of behaviour change for the patient and the therapist and these concepts will be core to the therapist education, prior to My Therapy implementation, as well as core to the My Therapy patient education provided by the therapists.

**Fig. 2 Fig2:**
[figure not shown]
The Why, What and How of behaviour change for the patient and the therapist

### Outcomes

#### Clinical evaluation

The primary clinical outcome is *functional independence*, which will be assessed using the Functional Independence Measure (FIM™) [37, 38]. The change in FIM™ from admission to discharge will be reported as the pro-portion of patients who achieve a MCID in FIM™ (22 points) [37]. The FIM™ is routinely recorded on admission and discharge from rehabilitation by accredited assessors, and will be used to report an overall score and sub-categories of motor and cognitive function.

Secondary outcomes include change in *health-related quality of life*, assessed using the EQ-5D-5L [39]; *rehabilitation length of stay*, reported as the number of overnight stays between the rehabilitation admission and discharge dates; *days at home up to 30 days after surgery (DAH30)* for any surgical patients [40, 41]; hospital re-admissions to the same health service one month (30 days) post-discharge (yes/no); discharge accommodation, categorised as home, transitional care, residential care, hospital, or death (no accommodation); need for post-discharge rehabilitation services (yes/no); and adverse events (falls), assessed as the number of falls and the number of serious falls during the rehabilitation admission, and these will be classified as occurring during or not during My Therapy participation.

#### Economic evaluation

For the economic evaluation, all cost data will be inflated to AUD$ 2021/22 (final year of data collection) using the consumer price index (CPI) (http://www.abs.gov.au/ausstats), and will take a health-care sector perspective, with a rehabilitation admission and 30-day re-admission time horizon. Discount rates will not be applied due to the limited time horizon. Six months after the end of the 2022 financial year (i.e., December 2022), all data will be available from the costing unit of each participating health service.

The primary economic outcome is the *incremental cost-effectiveness ratio (ICER)*, comparing the intervention and control groups using the health service cost, including 30-day re-admissions, as the numerator, and the utility data (quality adjusted life years (QALYs)) or effectiveness data (FIM™) as the denominator. A secondary economic outcome is the *cost of implementation* which will be recorded to inform future adoption and scaling of My Therapy and to understand the cost of the My Therapy intervention, independent of the health service costs for each rehabilitation patient (details in data analysis section).

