**Methods:**

This implementation trial aims to determine both the clinical effectiveness of My Therapy on the outcomes of function and health-related quality of life, and cost-effectiveness per minimal clinically important difference (MCID) in functional independence achieved and per quality adjusted life year (QALY) gained, compared to usual care. Using a stepped-wedge cluster randomised design, My Therapy will be implemented across eight rehabilitation wards (inpatient and home-based) within two public and two private Australian health networks, over 54-weeks. We will include 2,160 patients aged 18 + years receiving rehabilitation for any diagnosis. Each ward will transition from the usual care condition (control group receiving usual care) to the experimental condition (intervention group receiving My Therapy in addition to usual care) sequentially at six-week intervals. The primary clinical outcome is achievement of a MCID in the Functional Independence Measure (FIM™) at discharge. Secondary outcomes include improvement in quality of life (EQ-5D-5L) at discharge, length of stay, 30-day re-admissions, discharge accommodation, follow-up rehabilitation services and adverse events (falls). The economic outcomes are the cost-effectiveness per MCID in functional independence (FIM™) achieved and per QALY gained, for My Therapy compared to usual care, from a health-care sector perspective. Cost of implementation will also be reported. Clinical outcomes will be analysed via mixed-effects linear or logistic regression models, and economic outcomes will be analysed via incremental cost-effectiveness ratios.

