#### Statistical analyses

Analyses will only include data from patients who were admitted and discharged during the ward’s control condition period or experimental condition period. Patients still admitted to the rehabilitation wards at the end point of the study will not be included. It is expected that due to the step-wedged design, this will equally exclude long-stayers in the control and experimental condition periods. Each analysis will use individual patient-level data, clustered within the ward, and will use the length of time (in weeks) of experimental exposure as an effect modifier [32]. Length of time of exposure to the experimental condition is an important consideration when an intervention may take time to settle into usual practice and where there may be a cumulative effect [32]. Analyses will be conducted on an intention-to-treat basis.

The analyses will compare the FIM™ and the health-related quality of life utility index score between the control and the intervention groups. Health-related quality of life scores from the EQ-5D-5L will be converted from raw scores to a utility index based on an Australian population [46, 47]. The proportion of people who achieve a MCID of 22 points in FIM™ [35, 37] will be analysed using mixed effects logistic regression, and the change in FIM™ score and utility index will be ana-lysed using mixed effects linear regression. Length of stay will also be analysed via a linear regression model.

While not powered for a secondary analysis, there will be an exploratory secondary analysis of the same outcome measures within each of the clusters and for the two home-based bed-substitution wards. Other secondary outcomes will be compared between groups using univariable analyses. All outcomes will be reported with 95% confidence intervals and analyses will assume a significance of *p* < 0.05.

For the economic evaluation, the primary outcome will be presented as cost-effectiveness and cost-utility analyses, reporting (i) the cost per MCID in FIM™ achieved; and (ii) the cost per QALY gained. Costs will include the rehabilitation length of stay, acute transfers within the rehabilitation stay and unplanned re-admissions within the 30 days post discharge. The QALYs will be calculated using the utility index scores.

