The mean cost difference will be determined between the two groups using a linear regression model [48]. Incremental cost-effectiveness ratios will be determined for both the FIM™ and utility index using the cost as the numerator, and the utility or effectiveness data as the denominator. All analyses will use individual patient-level data, will be clustered within the ward, and will use the length of time (in weeks) of experimental exposure as an effect modifier [32]. The ICERs for the cost per MCID achieved will be analysed using mixed effects logistic regression, and the ICERs for the cost per QALY gained will be analysed using mixed effects linear regression. Confidence intervals around the individual ICERs for utility and effectiveness will be calculated using the bootstrap method with 5,000 repetitions [49]. Individual ICERs will use the central limit theorem to generate the confidence ellipses, and the cost effectiveness acceptability curves (CEACs) [49] to inform the probability that My Therapy is less costly and more beneficial compared with usual care alone, with a $50,000 per QALY gained [50] threshold to determine cost-effectiveness.

A cost-analysis will be utilised to determine the cost of implementation. Data will be presented within two time periods; (i) the preparation period while under usual care conditions as well as the three months prior to commencing My Therapy (e.g., materials purchased and staff education sessions), and (ii) the implementation period while under experimental conditions (from commencement of My Therapy through to the end of the inpatient data collection indicating business as usual). Periods (i) and (ii) together will represent the full cost of My Therapy implementation (i.e., preparation, implementation and transition to business-as-usual conditions), whereas just period (ii) will represent the costs under business-as-usual conditions (i.e., just implementation and transition to business-as-usual conditions).

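### The cost-per-QALY denominator is called both the utility index and a QALY derived from it, and no common time window is fixed, so the $50,000 threshold is either off scale or tied to length of stay

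*Protocol article*

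**What the plan says.** Under Outcomes, Economic evaluation, the primary economic outcome is a ratio with health service cost on top and "the utility data (quality adjusted life years (QALYs)) or effectiveness data (FIM™) as the denominator". The same section states the evaluation "with a rehabilitation admission and 30-day re-admission time horizon".

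Under Data Analysis, Statistical analyses, the article first says "The QALYs will be calculated using the utility index scores", which implies a conversion. It then says "Incremental cost-effectiveness ratios will be determined for both the FIM™ and utility index using the cost as the numerator", which names the index itself. The acceptability curves are read "with a $50,000 per QALY gained [50] threshold to determine cost-effectiveness".

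On timing, the costs run past discharge: "Costs will include the rehabilitation length of stay, acute transfers within the rehabilitation stay and unplanned re-admissions within the 30 days post discharge". The abstract gives the quality-of-life outcome as "improvement in quality of life (EQ-5D-5L) at discharge", and no later EQ-5D-5L assessment is described. The hypothesis at the end of the Background is that My Therapy will be cost-effective because it shortens the rehabilitation stay.

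**The concern.** A utility index has no time dimension. A QALY is utility multiplied by time, and a threshold in dollars per QALY has meaning only on that scale. Two places in the article treat the index and the QALY as the same denominator, and one place separates them. An analyst who follows the first two would compare cost per utility point with a threshold for cost per QALY.

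An analyst who follows the third has to choose a time window. The only horizon the article offers ends 30 days after each patient's own discharge. Its length therefore depends on an outcome the intervention is expected to reduce. What is at stake is the cost-utility half of the primary economic outcome and the probability of cost-effectiveness at $50,000.

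**Working it through.** The article gives no utility difference, cost difference, QALY or ratio, so there is no stated figure to reproduce.

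**Inputs from the article:** planning length of stay 18.5 days (Sample size calculation); cost follow-up 30 days after discharge; threshold $50,000 per QALY. Stay plus 30 days is 18.5 + 30 = 48.5 days.

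**Assumptions, not in the article:** utility gain 0.02 to 0.10; extra cost $1,000 for illustration; admission and discharge utility from 0.3 and 0.5 up to 0.5 and 0.7; stay shortened by 1 to 4 days. A year is 365.25 days.

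**First reading: the utility difference is the denominator.**

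- Constant difference over 48.5 days: QALY = gain × 48.5/365.25 = gain × 0.1328. Overstatement 365.25/48.5 = 7.5.
- Linear build over the stay, then held for 30 days: equivalent days 18.5/2 + 30 = 39.25; QALY = gain × 39.25/365.25 = gain × 0.1075. Overstatement 365.25/39.25 = 9.3.

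The largest extra cost that passes the threshold is $50,000 × QALY gain:

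| Assumed utility gain | Utility used as QALY | Time-weighted (linear build to constant) |
|---|---|---|
| 0.02 | $1,000 | $107 to $133 |
| 0.05 | $2,500 | $269 to $332 |
| 0.10 | $5,000 | $537 to $664 |

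With an extra cost of $1,000 and a gain of 0.05, the ratio is 1,000/0.05 = $20,000 per utility point. Time-weighted, it is 20,000 × 7.531 = about $151,000 to 20,000 × 9.306 = about $186,000 per QALY. The first lies below the threshold and the other two above it.

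**Second reading: utility is integrated over stay plus 30 days.** QALY = [stay × (admission + discharge utility)/2 + days after discharge × discharge utility]/365.25. With utilities of 0.4 and 0.6 in both groups:

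- 18.5-day stay: (18.5 × 0.5 + 30 × 0.6)/365.25 = 27.25/365.25
- 16.5-day stay, patient's own window: (16.5 × 0.5 + 30 × 0.6)/365.25 = 26.25/365.25, a difference of -1.00/365.25 = -0.0027
- 16.5-day stay, common 48.5-day window: (16.5 × 0.5 + 32 × 0.6)/365.25 = 27.45/365.25, a difference of +0.20/365.25 = +0.0005

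The discharge-utility gain needed to offset the loss in the patient's own window is days saved × mean utility over the stay, divided by (shortened stay/2 + 30). Here that is 2 × 0.5/38.25 = 0.026. Across the assumed utilities:

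| Days saved | Patient's own window | Common 48.5-day window | Gain needed to break even |
|---|---|---|---|
| 1 | -0.0011 to -0.0016 | +0.0003 | 0.010 to 0.015 |
| 2 | -0.0022 to -0.0033 | +0.0005 | 0.021 to 0.031 |
| 3 | -0.0033 to -0.0049 | +0.0008 | 0.032 to 0.048 |
| 4 | -0.0044 to -0.0066 | +0.0011 | 0.043 to 0.064 |

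**The case against.** The best defence is that the article does separate the two quantities in one sentence, names the outcome as cost per QALY throughout, and may intend the parenthesis in the outcome definition as shorthand. Interpolation and carry-forward rules are ordinarily left to an analysis plan. That much is fair: the text is inconsistent and does not uniformly equate utility with QALYs. Missing interpolation detail would not by itself be a finding. What remains is that the stated denominator, taken literally, does not match the stated threshold.

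It can also be said that the horizon sentence has cost data as its grammatical subject, and that nowhere does the article say QALYs accumulate over stay plus 30 days. This is correct, so the length-of-stay effect is conditional. But no other horizon is given.

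A reader might infer three stronger things that the document does not support:

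- *That both faults occur at once.* They cannot. If the index is the denominator, time does not enter and a shorter stay loses nothing. If utility is integrated over time, the threshold is on the right scale.
- *That the overstatement is about 39-fold.* That is 365.25/(18.5/2), which stops counting at discharge and ignores the 30 further days in the stated horizon.
- *That the result will have the wrong sign.* Rescaling utility cannot change a sign. Under the second reading the sign turns only if the discharge-utility gain is below break-even, for example 0.026 for 2 days saved; above that, the benefit is understated but still positive.

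**Conclusion.** The point holds as an inconsistency with two alternative consequences. Using utility directly overstates the denominator about 7.5- to 9.3-fold at an 18.5-day stay plus 30 days. Integrating over stay plus 30 days charges My Therapy for a shorter stay: about -0.0027 QALY for 2 days at utilities of 0.4 to 0.6, where a common 48.5-day window gives about +0.0005.

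The factors rest on the planning length of stay and on discharge utility persisting for 30 days. The dollar and QALY amounts rest on assumed utilities, costs and days saved. If My Therapy proves cheaper and better, the first reading leaves that dominance unchanged, but the acceptability probability at $50,000 would still move. The primary clinical outcome and its sample size are not affected.

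**What to change.** Reconcile the outcome definition under Economic evaluation with the two statements under Statistical analyses, and remove the wording that makes utility and QALYs interchangeable. Define QALYs as area under the utility curve over one fixed window from admission, the same for every patient and chosen so that the collected cost data cover it as far as possible. Interpolate linearly from admission to discharge utility, carry discharge utility forward to the end of the window, and adjust for admission utility. Vary the carry-forward assumption and the window length in sensitivity analyses.

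This is a change of wording and analysis that uses the utilities and costs already planned. It has two costs. The assumption about utility after discharge becomes explicit, and the trial's own data cannot test it. Cost cover will also be incomplete for some patients: costs stop 30 days after discharge, so very short stays may end before the window does, and very long stays run beyond it. A window much longer than 48.5 days would outrun the cost data for a patient with the planning length of stay.
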